### **9.3. Patient Disposition**

The Investigator will be responsible for maintaining a screen log and reason for non inclusion will be recorded. This will be maintained and will be provided to the Sponsor at regular intervals throughout the study and the totality at the end of the study.

The number of patients recruited and receiving study drug will be presented by treatment group, as will be the number of patients included in the various analysis populations.

Protocol violations will be listed per patient, describing the nature of the violation and specifying whether it is a major or a minor violation.

### **9.4. Determination of Sample Size**

Assuming a cure rate on Day 14 of 90% in both treatment groups and assuming a non-inferiority limit of -10%, then a sample size of 410 evaluable patients randomized in 1:1 ratio (205 patients in each treatment group) would provide 90% power to demonstrate non-inferiority of PA compared to the chloroquine, using a two-sided 95% confidence interval with Normal approximation. Assuming a drop out rate of 10%, 456 subjects would be randomized to the study (228 subjects in each treatment group).

Assuming a cure rate on Day 14 of 95%, this sample size would provide >99% power to demonstrate non-inferiority of PA compared to the chloroquine.

Sample size estimation was performed using nQuery statistical software version 4.0.

## 9.5. Statistical Evaluation

### 9.5.1. Efficacy and safety endpoints

Patient outcome will be classified according to WHO "Monitoring antimalarial drug resistance- Report of a WHO consultation Geneva, Switzerland, 3-5 December 2001".

#### Primary Efficacy Endpoint

The primary efficacy endpoint for the study is the cure rate on Day 14.

Cure on Day 14 will be defined as no parasitemia on Day 14 irrespective of axillary temperature without previously meeting any of the criteria of treatment failure throughout the follow-up period.

Treatment failure is defined as any of the following:

- ◆ Clinical deterioration due to *P. vivax* illness requiring hospitalization in presence of parasitemia.
- ◆ Presence of parasitemia and axillary temperature  $\geq 37.5^{\circ}\text{C}$  any time between Day 3 and Day 28.
- ◆ Presence of parasitemia on any day between Day 7 and Day 28 irrespective of clinical condition.

Patients presenting a *P. falciparum* infection after clearance of *P. vivax* parasites should be treated accordingly and withdrawn. They should not be considered as *P. vivax* treatment failures.

#### Secondary Efficacy Endpoints

The secondary efficacy endpoints are:

- Cure rate on Day 21 and Day 28, defined in the same way as cure rate on Day 14.
- Parasite Clearance Time (PCT).

Parasite clearance time is defined as the time from first dosing to time of first blood draw with parasite clearance. Parasite clearance

is defined as zero presence of asexual parasites for two consecutive negative readings taken between eight and twenty-four hours apart.

➤ **Fever Clearance Time (FCT)**

Fever clearance time is defined as the time from first dosing to first normal reading of temperature ( $<37.5^{\circ}\text{C}$  taken axillary or tympanic) for two consecutive normal temperature readings taken between eight and twenty-four hours apart.

The method of temperature measurement must be the same (i.e. axillary, tympanic, oral or rectal) for all measures in the same patient. Those patients who are initially included on history of fever and who do not subsequently have a documented temperature reading of over  $37.5^{\circ}\text{C}$  (taken axillary or tympanic) during the 24 hours following initial dosing, will not be included in this endpoint analysis.

- Proportion of patients who have cleared parasites on Day 1, 2 and 3
- Proportion of patients who have cleared fever on Day 1, 2 and 3

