## Definitions

**Parasite clearance:** at least two consecutive negative smears for parasites obtained within an interval of 8 to 24 hours, post-dosing.

**Fever clearance:** at least two consecutive normal body temperature measurements obtained within an interval of 8 to 24 hours, post-dosing.

**Treatment failure:** the definition of treatment failure includes the following:

- ◆ Clinical deterioration due to *P. vivax* illness requiring hospitalization in presence of parasitaemia.
- ◆ Presence of parasitemia and axillary temperature  $\geq 37.5^{\circ}\text{C}$  any time between Day 3 and Day 28.
- ◆ Presence of parasitemia on any day between Day 7 and Day 28 irrespective of clinical condition.

**Cure on Day 14:** no parasitaemia on Day 14 irrespective of axillary temperature without previously meeting any of the criteria of treatment failure.

**Cure on Day 28:** no parasitaemia on Day 28 irrespective of axillary temperature without previously meeting any of the criteria of treatment failure.

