##### 3.2.1. Inclusion criteria

Patients must fulfil the following inclusion criteria to be eligible for enrolment in the study:

1. Male or female patients between the age of 3 and 60 years, inclusive.
2. Body weight between 20 kg and 90 kg with no clinical evidence of severe malnutrition.
3. Presence of acute uncomplicated *P. vivax* mono-infection confirmed by:

- a. Fever, as defined by axillary/tympanic temperature  $\geq 37.5^{\circ}\text{C}$  or oral/rectal temperature  $\geq 38^{\circ}\text{C}$ , or history of fever in the previous 24 hours (history of fever must be documented) **and**,
  - b. Positive microscopy of *P. vivax* with parasite density  $\geq 250/\mu\text{L}$  of blood (including at least 50% of asexual parasites)
4. Written informed consent, in accordance with local practice, provided by patient and/or parent/guardian/spouse. If the patient is unable to write, witnessed consent is permitted according to local ethical considerations.
5. Ability to swallow oral medication.
6. Ability and willingness to participate based on information given to patient or parent or guardian and access to health facility.

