### **5.1.2. Clinical efficacy assessments**

#### **5.1.2.1. Body temperature**

Body temperature will be measured at screening on Day 0 (Pre-Dose) and every 8 hours over at least 72 hours following first study drug administration or when fever has normalised ( $<37.5^{\circ}\text{C}$  axillary/tympanic or  $<38^{\circ}\text{C}$  oral/rectal): 2 normal readings taken between 8 and 24 hours apart. Temperature will be measured at every visit thereafter and as clinically indicated.

Temperature methodology shall be according to local practice. For each individual patient, the same means of temperature measure (axillary, oral, tympanic, rectal) should be used throughout the entire study period. Patients who have had a documented reported history of fever ( $\geq 37.5^{\circ}\text{C}$  axillary/tympanic or  $\geq 38.0^{\circ}\text{C}$  oral/rectal) prior to screening should be monitored closely for fever peaks.

Patients entered in the study on the basis of history of fever and who do not subsequently have at least one body temperature measurement indicating presence of fever will not be included in the analysis of fever clearance time.

Quality of temperature-taking technique and thermometers should be checked and calibrated prior to study commencement and at regular intervals during study.

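### Fever clearance time has two conflicting analysis sets for patients enrolled on history of fever, and its definition lets clearance be scored before the qualifying fever appears

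*Protocol*

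**What the plan says.** - **Entry (Protocol 3.2.1).** A measured fever is not required; the criterion also accepts a documented history: "or history of fever in the previous 24 hours". A patient can be afebrile at dosing.
- **Endpoint (9.5.1, Secondary Efficacy Endpoints).** "Fever clearance time is defined as the time from first dosing to first normal reading of temperature", the confirmation being "for two consecutive normal temperature readings taken between eight and twenty-four hours apart".
- **Definitions.** Fever clearance is "at least two consecutive normal body temperature measurements obtained within an interval of 8 to 24 hours, post-dosing". No earlier fever is required here either.
- **Analysis set in 9.5.1.** History-of-fever patients with no reading over 37.5 °C (axillary or tympanic) "during the 24 hours following initial dosing, will not be included in this endpoint analysis".
- **Analysis set in 5.1.2.1.** For patients enrolled on history of fever, the exclusion reads: "do not subsequently have at least one body temperature measurement indicating presence of fever will not be included in the analysis of fever clearance time". There is no time window, and fever in that section is 37.5 °C or higher axillary/tympanic, or 38.0 °C or higher oral/rectal.
- **Readings (5.1.2.1).** Temperature is taken "every 8 hours over at least 72 hours following first study drug administration or when fever has normalised".
- **Analysis (9.5.2).** Kaplan-Meier medians and quartiles with a log-rank test. Only patients without documented clearance are censored. Fever that begins after two normal readings is not addressed.

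**The concern.** Two sections give explicit exclusion rules for the same analysis, and the rules differ. A history-only patient whose first fever is seen at 32 hours is in the FCT analysis under 5.1.2.1 and out of it under 9.5.1. The thresholds differ too. Section 9.5.1 gives no oral or rectal cut-off although both methods are allowed. It also requires a reading over 37.5 °C while calling only readings below 37.5 °C normal, so a reading of exactly 37.5 °C is neither normal nor qualifying there. Under 5.1.2.1 it is fever.

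The endpoint rule adds a separate defect. A history-only patient is analysed because a fever was later recorded, but the clock can stop at a pair of normal readings taken before that fever. The score is then the earliest one the schedule allows, however late or long the fever. FCT and the proportions with fever cleared on Days 1, 2 and 3 are listed secondary endpoints. Two analysts who each follow the protocol could report different populations and different medians.

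**Working it through.** The plan states no figure on this point, so the check applies the written rule to the written schedule.

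**Inputs.** Post-dose readings at 8, 16, …, 72 h (5.1.2.1). Patient afebrile at entry (allowed by 3.2.1), with one febrile reading at time f and all others normal. Scored FCT is the earliest time a such that a and a + 8 h are both normal; an 8-hour gap satisfies the 8-to-24-hour condition. Only post-dose readings count, as in the Definitions. (Section 9.5.1 does not itself exclude the pre-dose reading; if that counted, f = 16 h or later would score 0 h.) A reading at 24 h is taken as inside the 9.5.1 window.

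| First fever f | FCT as written | In 9.5.1 set | In 5.1.2.1 set | FCT from dosing, normals after the fever | Same, clock from first fever |
|---|---|---|---|---|---|
| 8 h | 16 h | yes | yes | 16 h | 8 h |
| 16 h | 24 h | yes | yes | 24 h | 8 h |
| 24 h | **8 h** | yes | yes | 32 h | 8 h |
| 32 h | **8 h** | no | yes | 40 h | 8 h |
| 40 h | **8 h** | no | yes | 48 h | 8 h |
| 48 h | **8 h** | no | yes | 56 h | 8 h |
| 56 h | **8 h** | no | yes | 64 h | 8 h |
| 64, 72 h | **8 h** | no | yes | not documented by 72 h | not documented by 72 h |

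**Reading the table.**

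1. For f = 8 or 16 h no two normal post-dose readings precede the fever, so the written rule gives the right order of events.
2. For f = 24 h the pair at 8 and 16 h is complete before the fever. Scored clearance precedes the fever by 24 − 8 = 16 h.
3. For f = 32 to 72 h it precedes the fever by 32 − 8 = 24 h up to 72 − 8 = 64 h. These patients are analysed only under 5.1.2.1.
4. The 8 h score does not respond to the fever's length. If the patient is febrile at 24, 32, 40 and 48 h and normal at 56 and 64 h, the written rule still gives 8 h. Clearance after the fever is at 56 h from dosing, or 56 − 24 = 32 h from the first recorded fever. The 8 h values in the last column match the written score only because the example has a single febrile reading.
5. Censoring in 9.5.2 does not help, because these patients do have a documented pair of normal readings.

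**Share affected.** Let h be the history-only share, which the documents do not give. Assume every such patient becomes febrile, with first fever equally likely at 8, 16, …, 48 h (six times).

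- Dropped under 9.5.1 (first fever at 32, 40 or 48 h): 3h/6.
- Mis-scored among those kept under 9.5.1: (h/6)/(1 − h/2).
- Mis-scored under 5.1.2.1 (first fever at 24 h or later): 4h/6.

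At h = 30%: 15% dropped; 0.05/0.85 = 6% mis-scored under 9.5.1; 20% under 5.1.2.1. At h = 15%: 7.5%; 0.025/0.925 = 3%; 10%. These show how the two sections differ. They do not estimate what will happen in the trial.

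**The case against.** **Scope.** A reader might infer that every patient who enters afebrile and later becomes febrile is mis-scored. The table does not support that: fevers at 8 and 16 h are handled correctly, and the 24-hour window in 9.5.1 excludes nearly all the rest. This stands.

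**Size.** A reader might infer that medians are wrong by 8 to 11 hours. An illustrative simulation used the assumptions above with h = 30%, 228 patients per arm, and time from fever to clearance exponential with medians 16 and 22 h. It gives about 21 vs 25 h under 9.5.1 as written, and 29 vs 36 h if all history-only patients are kept and normals must follow the fever. That contrast changes set and rule together. With the 9.5.1 set held fixed, the rule alone moves 21 vs 25 h to about 24 vs 30 h, less than one 8-hour reading interval. Patients febrile at entry have medians of about 20 and 25.5 h in the same model, so 29 vs 36 h is no true value either: it counts afebrile time before onset as uncleared fever. The inputs have no source in the protocol.

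**Inference.** A reader might infer that the comparison between arms is compromised. In the same simulation log-rank power stays between 80% and 84% under all three scorings, with the same direction throughout. This objection stands.

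**Monitoring.** A reader might infer that detection of late fever depends on the site, because 5.1.2.1 and note b of Attachment 2 allow 8-hourly readings to end once temperature is normal. But Section 6 schedules 8-hourly readings on Days 0 to 3 with no stopping rule, and 5.1.2.1 asks for close watch on history-of-fever patients. The texts are ambiguous; variation between sites is not shown.

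**Left to the SAP.** Derivation detail often is. Here, however, the protocol itself states two incompatible exclusion rules and a derivation that, taken literally, puts clearance before fever. Section 9 requires departures from the planned analysis to be justified and recorded, so the wording needs correcting at its source.

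**Conclusion.** Both defects stand on the protocol's text. The FCT analysis set is defined in two incompatible ways for history-of-fever patients. The clearance rule also lets a patient with two normal post-dose readings before the first fever be scored as cleared, at 8 h on the scheduled grid, before that fever exists. Under 9.5.1 this reaches only a first fever at about the 24-hour reading; under 5.1.2.1, any first fever from 24 hours onward.

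The size of the bias cannot be calculated without the history-only share and the timing of later fevers. For affected patients the direction is downward, since 8 h is the earliest score the post-dose schedule allows. The consequence is for reported FCT medians and, if the same rule is used, the Day 1 to 3 fever-clearance proportions. The Day 14 cure rate is not affected, and nothing here shows that the FCT comparison between arms would change. It is worth correcting because a listed secondary endpoint is ambiguous and the repair is small.

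**What to change.** 1. Reconcile 5.1.2.1 and 9.5.1 to one FCT analysis set with one time window and the same thresholds for each measurement method, including oral and rectal, with one convention for a reading of exactly 37.5 °C.
2. In the Definitions and 9.5.1, require the two consecutive normal readings to follow a recorded fever. Apply the same rule to the proportions with fever cleared on Days 1, 2 and 3.
3. For history-only patients, choose one of two options so that afebrile time before onset is not counted as uncleared fever. Either start the clock at the first recorded fever, or restrict the main FCT analysis to patients febrile at baseline and report history-only patients in a sensitivity analysis.
4. State that the 8-hourly readings already scheduled on Days 0 to 3 in Section 6 are completed to 72 hours in history-only patients.

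The cost is wording in three places and one derivation rule. Patients are already confined on Days 0 to 3, so any added burden is a few temperature readings. The first option in item 3 mixes time origins within one Kaplan-Meier curve; the second makes the main FCT set slightly smaller.

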#### **Secondary Efficacy Analyses:**

The primary efficacy analysis performed on Day 14 will be repeated for the proportion of patients with cure on Day 21 and 28, using the efficacy evaluable population.

In addition, the analysis performed using the EE population will be repeated using the ITT population.

The parasite clearance time and fever clearance time will be analysed using Kaplan-Meier estimates. The median and quartiles clearance time will be presented together with the corresponding 95% confidence intervals. The mean will also be calculated. The survival curves will be presented. The log rank test will be used to compare the parasite clearance time and fever clearance time between the two treatment groups. Patients who do not have documented parasite or fever clearance will be censored. Censoring time will be greater than the highest observed clearance time.

The proportion of patients who have parasite clearance and the proportion of patients who have fever clearance will be presented at Day 1, Day 2 and Day 3. The associated exact 95% confidence interval will also be calculated.

The number of parasites will be summarized using standard descriptive statistics, as well as geometric mean and its associated 95% confidence interval using an analysis of variance model on  $\log_{10}$  transformed parasites counts with treatment and site as factors. The mean parasite count at each scheduled timepoint will be presented graphically.

All secondary efficacy analyses will be performed both on the EE and ITT populations.

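### The Day 1, 2 and 3 fever-clearance proportions count patients who were never febrile on study as cleared, so the reported rates are inflated

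*Protocol*

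**What the plan says.** Four parts of the Protocol bear on this.

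- **Entry.** Inclusion criterion 3a (section 3.2.1) accepts either a measured fever or a documented "history of fever in the previous 24 hours". A patient can therefore be randomised with a normal temperature.
- **Definition of clearance.** The Definitions page describes fever clearance as "at least two consecutive normal body temperature measurements obtained within an interval of 8 to 24 hours, post-dosing". It does not require a febrile reading to come first.
- **Exclusion of never-febrile patients.** Section 5.1.2.1 says that patients who entered on history and show no later febrile reading "will not be included in the analysis of fever clearance time". The fever clearance time (FCT) item of section 9.5.1 says that history-only patients without a reading over 37.5°C (axillary or tympanic) "during the 24 hours following initial dosing, will not be included in this endpoint analysis". Both statements concern FCT.
- **The proportions.** "Proportion of patients who have cleared fever on Day 1, 2 and 3" is a separate bullet in section 9.5.1, with no exclusion attached. Section 9.5.2 says that "the proportion of patients who have fever clearance will be presented at Day 1, Day 2 and Day 3", with an exact 95% confidence interval, and adds: "All secondary efficacy analyses will be performed both on the EE and ITT populations". Neither population, as defined in section 9.2, requires a fever.

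**The concern.** A patient who enters with a normal temperature and stays normal has no fever to clear. The protocol recognises this for FCT and removes such patients. It does not do so for the Day 1, 2 and 3 proportions, where the stated definition scores them as successes without any drug effect.

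The reported proportions would then mix the speed of fever clearance with the share of patients enrolled on history alone. They would be too high in both arms and would sit closer together than the rates among febrile patients. They would also be reported beside an FCT analysis of the same symptom that uses different patients.

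**Working it through.** **Plan's own figure.** The protocol gives no expected fever-clearance proportion and no share of patients without fever, so there is nothing to reproduce for this endpoint. The sample size in section 9.4 concerns the Day 14 cure rate. A restricted-variance (Farrington-Manning) calculation gives 204.3, so 205 per arm, and 410/0.9 = 455.6, so 456 randomised. This point does not affect it.

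**Step 1: apply the definition to one patient.** Entry temperature 36.8°C on a history of fever, then 36.9°C at 8 h, 36.8°C at 16 h, and never febrile afterwards. The 8 h and 16 h readings are two consecutive normal readings 8 hours apart, so the patient is cleared on Days 1, 2 and 3. Under sections 5.1.2.1 and 9.5.1 the same patient is left out of FCT.

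**Step 2: effect on the proportions.** Let h be the share never febrile on study and p the clearance rate among the rest.

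- Reported proportion = h×1 + (1−h)×p = h + (1−h)p, an inflation of h(1−p).
- Reported difference with equal h = (1−h)(p₁ − p₂).

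**Step 3: numbers.** Both h and p are assumptions. With p of 80% and 60% (a 20-point difference):

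| h | Reported, arm 1 | Reported, arm 2 | Difference |
|---|---|---|---|
| 10% | 82% | 64% | 18 points |
| 20% | 84% | 68% | 16 points |
| 30% | 86% | 72% | 14 points |
| 40% | 88% | 76% | 12 points |
| 50% | 90% | 80% | 10 points |

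For h = 30%: 0.30 + 0.70×0.80 = 0.86 and 0.30 + 0.70×0.60 = 0.72. If clearance is nearly complete in both arms (98% and 95%), the 3-point difference falls to 2.7 points at h = 10% and 1.5 points at h = 50%.

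**Step 4: unequal h.** Randomisation balances fever at entry in expectation. Never febrile on study also depends on post-dose readings, which treatment can change. With p of 80% and 60%:

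- h of 35% and 25%: 0.87 − 0.70 = 17 points.
- h of 25% and 35%: 0.85 − 0.74 = 11 points.

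The factor (1−h) is therefore exact only when h is the same in both arms.

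**Step 5: a separate flaw in the clearance rule.** Take entry 36.8°C, then 36.9°C at 8 h, 36.8°C at 16 h and 38.6°C at 24 h. This patient has a fever within 24 hours of dosing and so stays in FCT, yet clearance is dated to 8 h, before the fever. To gauge how often this could happen, assume an independent chance f of fever at each of 8, 16 and 24 h in history-only patients. Among those with any fever by 24 h, the share with first fever at 24 h is (1−f)²f / (1 − (1−f)³):

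- f = 0.2: 0.128/0.488 = 26.2%
- f = 0.3: 0.147/0.657 = 22.4%
- f = 0.5: 0.125/0.875 = 14.3%

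**The case against.** The strongest reply is that no sentence says never-febrile patients are counted in the proportions. The statement about EE and ITT also covers FCT, which still drops such patients, so naming those populations does not by itself settle the denominator. To speak of clearing fever can be read as presupposing a fever. The protocol defers detail to a statistical analysis plan that was not available for this check and could extend the exclusion.

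Part of this stands: the inclusion is inferred. But the inference rests on rules the protocol does state. It defines clearance without a prior fever, and it confines the exclusion to FCT in two places. An analyst who follows the text counts these patients, so this is more than detail left open.

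A reader might infer four stronger things that the documents do not support:

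- **That a planned comparison of the arms is compromised.** Section 9.5.2 plans only exact 95% intervals for these proportions. The log-rank test on fever uses FCT, from which never-febrile patients are removed. Even if the proportions were tested with 205 per arm, little power would be lost: 93.9% over all patients against 96.2% among febrile patients at h = 30%, with rates of 80% and 60%.
- **That the size of the distortion is known.** Every value of h and p above is assumed.
- **That differences between sites in history-only entry bias the contrast.** Section 4.1 assigns complete randomisation blocks to each site, so the mix at entry is balanced in expectation.
- **That the fever-at-24-h patient illustrates the denominator problem.** That patient is febrile on study, so the flaw lies in the clearance rule and affects FCT as well.

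**Conclusion.** The point holds in a limited form. As written, the Day 1, 2 and 3 fever-clearance proportions include patients who were never febrile on study and who meet the clearance definition automatically. Each arm's proportion is raised by h(1−p), and a descriptive contrast shrinks by about (1−h) if h is equal in the two arms. Over the assumed range of h from 10% to 50%, a 20-point difference would be reported as 18 down to 10 points.

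The effect is confined to secondary summaries for which no between-arm test is planned. The Day 14 cure rate and the sample size are unaffected. The correction is still worth making, because the reported rates would not measure clearance of fever and would not match the FCT analysis beside them.

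**What to change.** **Proportions.** In sections 9.5.1 and 9.5.2, state that the denominator of the Day 1, 2 and 3 fever-clearance proportions, within both EE and ITT, is patients with a documented fever at the pre-dose reading. This is a baseline condition that treatment cannot change. Copying the FCT exclusion instead would select patients on post-dose temperatures. No further rule about the order of readings is needed here, since every post-dose reading then follows a febrile one.

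**Fever clearance time.** Two separate edits:

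- Count clearance only from normal readings that come after a documented febrile reading.
- Reconcile section 5.1.2.1, which sets no time limit on the later febrile reading, with section 9.5.1, which limits it to 24 hours after the first dose.

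**Cost.** A few sentences and a filter on temperatures already collected. Fewer patients contribute, so the exact intervals widen. If 30% of patients had no pre-dose fever, 205 per arm would fall to about 144 (205×0.70 = 143.5), and intervals would be roughly 1/√0.70 ≈ 1.2 times as wide from sample size alone. The denominator would still differ from that of FCT, which keeps history-only patients who become febrile within 24 hours. The report should say so.
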